### Statistical analyses

All data will be analyzed by the SPSS software (version 26, IBM Corp., USA). Both the intention-to-treat analysis and the per-protocol analysis will be performed for the primary outcome. Subgroup analyses will be performed based on the values of the incidence of cough, hoarseness, and PONV; the intensity of POST; and NRS for pain intensity within 24 h after extubation. A two-sided significance level will be set at *P* < 0.05 for all statistical tests. The continuous variables will be expressed as a mean with standard deviation (normal distribution) or a median with interquartile range (skewed distribution). Student’s *t* test will be used to compare normally distributed continuous variables, and the Mann–Whitney *U* test will be used to compare non-normally distributed continuous variables. The categorical variables such as the incidence of sore throat, cough, hoarseness, and PONV within 24 h after extubation will be described as counts and percentages. Differences between the groups of these categorical variables will be compared with *χ*^2^ analysis or Fisher’s exact test. The missing data will be handled by multiple imputation.

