## Methods

### Study design

This is a single-center, parallel-group, randomized controlled, superiority trial with a 1:1 allocation ratio. The time schedule of the protocol (Table 1) is based on the Standard Protocol Items: Recommendations for Interventional Trials (SPIRIT) 2013 [15].

**Table 1 Tab1:** The schedule of enrollment, interventions, and assessments

	Study period			
	Enrollment	Allocation	Post-allocation (post-extubation)	
Time point	− 1 day before surgery	Day of surgery	0 h	24 h
Enrollment				
Eligibility screen	X			
Informed consent	X			
Allocation		X		
Interventions				
CPMA group		X		
Control group		X		
Assessments				
Baseline variables	X	X		
Number of patients with POST at rest			X	X
Number of patients with cough			X	X
Number of patients with hoarseness			X	X
Number of patients with PONV			X	X
Pain intensity (NRS)			X	X

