### Interventions

No preoperative medication will be used in all patients. After entering the operating room, patients will be routinely monitored for non-invasive arterial blood pressure, electrocardiogram, pulse oxygen saturation, end-tidal carbon dioxide, and then inhale oxygen through a mask. After peripheral venous catheterization, midazolam (0.02–0.05 mg/kg), sufentanil (0.2–0.5 μg/kg), propofol (2–3 mg/kg), and rocuronium (0.6–0.8 mg/kg) will be injected intravenously during induction of general anesthesia. The anesthesiologists with at least two years of experience will select polyvinyl chloride endotracheal tubes of 7.0 mm internal diameter for video laryngoscope-guided intubation. In the cuff pressure measurement and adjustment (CPMA) group, the anesthesiologist will connect the pressure transducer to the spring-loaded one-way valve of the pilot balloon through a three-way connector and then inflate or deflate the tube cuff with a syringe connected to a tee-junction to maintain 18–22 mmHg cuff pressure intraoperatively. In the control group, the tube cuff pressure will be adjusted by anesthesiologists’ experience with pilot balloon finger palpation before the operation and will not be adjusted during the operation but will be monitored blindly on the portable monitor which screen will be fully covered. The number of tracheal intubation attempts, cricoid compression, and cough during intubation will be recorded. After successful endotracheal intubation, volume-controlled ventilation will be performed with a tidal volume of 6–8 ml/kg, a respiratory rate of 12–18 breaths per minute, an inspiratory-to-expiratory ratio of 1:2, an inspired oxygen fraction of 80%, and a flow rate of 1–2 L/min to adjust end-expiratory carbon dioxide partial pressure to 35–45 mmHg. Total intravenous anesthesia will be maintained with propofol (4–6 mg/kg/h) and remifentanil (0.1–0.25 μg/kg/min). Additional rocuronium 10–20 mg and sufentanil 5–10 μg will be administered as needed during the operation. After the establishment of carbon dioxide pneumoperitoneum, the patients in both groups will be placed in the Trendelenburg position required for gynecological laparoscopic surgery. The pneumoperitoneum pressure will be kept at 14 mmHg. Hemodynamic changes will be monitored and recorded every 5 min during the operation. Operation time and endotracheal tube indwelling time will also be recorded. After the surgery, gentle suction of oropharyngeal secretions will be performed in both groups (the wall suction pressure ranges from − 80 to − 120 mmHg). The administration of intravenous muscle relaxant antagonist (neostigmine 40 μg/kg) will be determined based on the assessment of muscle strength recovery. Once the patient is fully awake, the tidal volume has been restored to normal, and sufficient oxygen saturation can be maintained, air will be withdrawn from the cuff, and the endotracheal tube will be removed. In addition, the number of coughs before extubation will be recorded. Both groups of subjects will receive postoperative pain control via an analgesic pump with sufentanil at a rate of 2 μg/h and a total dose of 100 μg. Sore throat at rest and its severity, cough, hoarseness, nausea and vomiting, and pain score will be recorded immediately after extubation (0 h after extubation) and within 24 h after extubation. The investigators will record conditions in which enrolled subjects are deemed unfit to proceed with the study due to the following reasons: occurrence of adverse events, including severe adverse events, and other circumstances identified by the researchers as unsuitable for further experimentation. To enhance participants’ adherence with the intervention measures, researchers will employ clear and comprehensible language to communicate with patients, conduct timely follow-ups, and engage in interactive discussions. The researchers will also record timely during the intervention and follow-up process to monitor the compliance of the subjects.

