
### Outcomes and measurements

#### Primary outcome

The primary outcome is the incidence of sore throat at rest within 24 h after extubation. The total number of patients with sore throat at rest between two assessment time points (0 h and 24 h post-extubation) will be recorded.

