#### Secondary outcomes

The secondary outcomes include the following: (1) the incidence of cough within 24 h after extubation; (2) the incidence of hoarseness within 24 h after extubation; (3) the incidence of PONV within 24 h after extubation; (4) the intensity of POST within 24 h after extubation graded on a 0–3 scale: 0 = no sore throat, 1 = mild sore throat (less pain than a cold), 2 = moderate sore throat (like a cold), and 3 = severe sore throat (more severe than a cold) [16–19]; and (5) 11-point Numerical Rating Scale (NRS) for pain intensity within 24 h after extubation: 0 = no pain and 10 = worst pain imaginable [20].

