### Assignment of interventions

#### Randomization

Participants will be randomly assigned to either the CPMA or the control group with a 1:1 allocation on the day of surgery using Ericure, which is a computer-generated central randomization online service [21]. Blocked randomization using permuted blocks of random sizes will reduce the predictability of the allocation sequence. The allocation sequence in the central randomization system will be managed by a statistician independent of the research. Blinded study personnel who are unaware of the allocation sequence will receive a randomization code via a central randomization system on the day of surgery, following subject screening and all baseline measurements, thereby ensuring allocation concealment. The allocation sequence will be concealed without the influence of selection bias until the completion of the database analysis.

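### The planned subgroups are defined by the trial's five secondary outcomes, so arm comparisons within them are not randomised comparisons, and the split by sore throat intensity shows no difference by construction

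*Protocol article*

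**What the plan says.** All references are to the protocol article.

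- **Statistical analyses:** "Subgroup analyses will be performed based on the values of the incidence of cough, hoarseness, and PONV; the intensity of POST". The sentence ends by adding the NRS pain score within 24 h after extubation. No baseline variable is named as a subgroup factor.
- **Secondary outcomes:** the list opens "The secondary outcomes include the following: (1) the incidence of cough within 24 h after extubation" and continues with hoarseness, PONV, sore throat intensity and NRS pain. These are the same five variables, in the same order and over the same time window.
- **Interventions:** sore throat at rest and its severity, cough, hoarseness, nausea and vomiting, and pain "will be recorded immediately after extubation (0 h after extubation) and within 24 h after extubation". Table 1 (Study design) agrees. For example, the row "Number of patients with hoarseness" is marked only at 0 h and 24 h after extubation.
- **Randomization:** "Participants will be randomly assigned to either the CPMA or the control group with a 1:1 allocation on the day of surgery". All five variables are therefore observed after allocation and after the intervention.
- **Primary outcome:** "The primary outcome is the incidence of sore throat at rest within 24 h after extubation".
- **Secondary outcomes, item 4:** "the intensity of POST within 24 h after extubation graded on a 0–3 scale: 0 = no sore throat". Grades 1 to 3 are mild, moderate and severe sore throat.

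**The concern.** A subgroup comparison keeps the protection of randomisation only if the subgroup is fixed before treatment can act on it. None of the five listed variables meets that condition. The trial lists each of them as an outcome on which the arms may differ. If cuff-pressure adjustment changes who becomes hoarse, hoarse patients in the CPMA arm and hoarse patients in the control arm are differently selected groups. A difference in sore throat between them mixes treatment effect with selection.

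Sore throat intensity is a special case, because it grades the symptom that the primary outcome counts. Stratifying the primary outcome by it amounts to stratifying the outcome by itself.

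What is at stake is the standing of the subgroup results. They would carry the label of pre-specified analyses in a 60-patient trial, yet could not be read as treatment effects.

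**Working it through.** The plan gives no figure for the subgroup analyses, so there is none to reproduce. The relevant planning inputs, from Sample size calculation, are sore throat rates of 32% (CPMA) and 68% (control) with 30 patients per arm. The planned difference is 68 − 32 = 36 points.

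**1. Sore throat intensity.** The one assumption is that the 0–3 grade rates the same sore throat at rest as the primary outcome. The Interventions section supports this, since it records sore throat at rest together with its severity.

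| Stratum | CPMA, expected n | Control, expected n | Primary incidence, CPMA | Primary incidence, control | Difference |
|---|---|---|---|---|---|
| Grade 0 | 30 × 0.68 = 20.4 | 30 × 0.32 = 9.6 | 0% | 0% | 0 |
| Grades 1–3 | 30 × 0.32 = 9.6 | 30 × 0.68 = 20.4 | 100% | 100% | 0 |

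The whole 36-point effect sits in how many patients fall in each stratum, and none of it remains within a stratum. This holds whatever the true effect is.

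**2. Hoarseness, worked example with no treatment effect on sore throat.** All inputs here are assumed; none is in the documents. Half the patients have a susceptible airway. Sore throat risk is 0.3 (not susceptible) or 0.8 (susceptible) in both arms, so the overall rate is 0.5 × (0.3 + 0.8) = 55% in each arm. Hoarseness risk is 0.4 or 0.8 in control, and 0.1 or 0.6 in CPMA.

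- Hoarse, control: 0.5 × (0.4×0.3 + 0.8×0.8) / 0.60 = 0.380 / 0.60 = 63.3%
- Hoarse, CPMA: 0.5 × (0.1×0.3 + 0.6×0.8) / 0.35 = 0.255 / 0.35 = 72.9%
- Not hoarse, control: 0.5 × (0.6×0.3 + 0.2×0.8) / 0.40 = 0.170 / 0.40 = 42.5%
- Not hoarse, CPMA: 0.5 × (0.9×0.3 + 0.4×0.8) / 0.65 = 0.295 / 0.65 = 45.4%

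The apparent differences against CPMA are 9.5 and 2.9 points. Both come from the conditioning alone.

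**3. Range over assumptions.** A normally distributed latent susceptibility, shared by sore throat and hoarseness, acts on the logit scale. Its SD was varied from 0 to 2.5. Intercepts were set so that each arm has the stated overall rates. Hoarseness (control/CPMA) was taken as 40/30%, 50/25% and 60/20%.

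| Overall sore throat, control vs CPMA | True difference | Range of within-stratum difference |
|---|---|---|
| 68% vs 32% (planned rates) | 36 points | 13.6 to 36.0 points |
| 50% vs 50% (assumed, no effect) | 0 | 0 to about 19 points, against CPMA |

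With SD 0 (no shared cause) there is no distortion. Within these inputs, distortion is largest with the strongest shared cause and the largest effect on hoarseness.

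**The case against.** The strongest reply is that the term subgroup analyses is a slip for the analysis of the secondary outcomes. The list reproduces secondary outcomes (1) to (5) in order and with the same time window, and it follows directly after the sentence on the primary outcome's analysis sets. It names no strata, no cut-point for the 0–10 NRS, no outcome to compare within strata and no interaction test. The degeneracy itself suggests that nobody meant to split sore throat by its own grade. The same section then gives ordinary between-group tests for the incidence outcomes and for continuous variables.

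Much of this stands. A reader might infer that the investigators certainly intend to stratify by these outcomes; the text does not establish that. But it does not state the benign meaning either. Its wording is that of stratification, and because the between-group tests are given separately, the sentence is not needed to introduce them. An analyst who followed it literally would run an unsound analysis.

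A reader might also infer that such results would be reported as effect modification. The article describes no such reporting. Nor does it state an expected effect of cuff pressure on cough or hoarseness: its hypothesis concerns sore throat only. That an effect on them is possible is inferred from their being listed as outcomes.

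**Conclusion.** The sentence needs correcting under either reading: as a stratification it is unsound, and as a description of the secondary analyses it is misnamed. The rating is should-fix.

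The firm part is structural. All five variables are post-randomisation outcomes, and the intensity split gives a zero difference in every stratum, provided the grade rates the same sore throat at rest. The size of bias for the other variables is not fixed by the documents. The 0 to about 19 points is for hoarseness, under an assumed shared cause and assumed hoarseness rates, and no single figure within it should be quoted as the bias.

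It would be wrong to conclude that the trial's main result is compromised. The intention-to-treat and per-protocol comparisons of the primary outcome, the sample size and the between-group tests of the secondary outcomes do not depend on this sentence, and no claim of success rests on a subgroup.

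**What to change.** Reword the sentence to say that cough, hoarseness, PONV, sore throat intensity and NRS pain within 24 h after extubation will be analysed as secondary outcomes, comparing the arms in all randomised patients. Rewording is better than deleting, because this is the only sentence in Statistical analyses that names sore throat intensity and NRS pain.

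If subgroup analyses of the primary outcome are wanted, define them only on variables fixed before randomisation (age or BMI, for example), test them with a treatment-by-subgroup interaction and label them exploratory.

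The cost is one sentence, filed under the article's own amendment procedure, with no added data or patients. The article has enrolment still in progress at submission and unblinding only after the database analysis is complete, so the change can be made without knowledge of results if it is made before that point.

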### Sample size calculation

The sample size estimation is based on the incidence of sore throat while resting within 24 h post-extubation. This superiority trial with a 1:1 allocation ratio will achieve 80% power (1 − β) and a one-sided significance level (*α*) of 0.025. In a randomized controlled study of gynecologic laparoscopic surgery [14], the incidence of POST was 31.7% (19/60) in cuff pressure adjusted to 25 cmH_2_O group (using the manometer) and 68.3% (41/60) in the control group (using palpation of the pilot balloon). Based on this study of a similar surgery, we estimate the incidence of sore throat at rest within 24 h post-extubation is 32% in the CPMA group and 68% in the control group. Then, 54 participants should be needed according to the conditions mentioned above. Eventually, a total of 60 patients (30 in each group) will be recruited so as to allow for a 10% dropout rate. The sample size was calculated using tests for two proportions in the PASS software (version 15, NCSS Corp., USA).

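### The test rules have no route for the ordinal 0–3 sore-throat grade; read literally, it falls to an unordered χ²/Fisher test

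*Protocol article*

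**What the plan says.** Under Secondary outcomes, item 4 is "the intensity of POST within 24 h after extubation graded on a 0–3 scale", with levels running from none through mild and moderate to severe.

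Statistical analyses then assigns tests by variable type:

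- **Continuous:** the t test if normal. Otherwise the Mann–Whitney "test will be used to compare non-normally distributed continuous variables".
- **Categorical:** the variables are introduced by example, as "The categorical variables such as the incidence of sore throat, cough, hoarseness, and PONV within 24 h after extubation", and summarised by counts and percentages. Then "Differences between the groups of these categorical variables will be compared with" χ² or Fisher's exact test.

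No third route is given for ordered categories. The grade is mentioned only once in that section, in the sentence "Subgroup analyses will be performed based on the values of the incidence of cough, hoarseness, and PONV; the intensity of POST", which names no test.

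**The concern.** A four-level verbal grade is ordered but not continuous. If the stated rules are applied as worded, Mann–Whitney is not available for it and the categorical route is what remains. A χ² or Fisher test on a 2×4 table treats the four grades as unordered labels. It asks whether the two distributions differ in any way, not whether one arm has milder sore throat.

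The trial's idea is directional in substance: controlling cuff pressure should reduce sore throat. A real shift toward milder grades would then be more likely to be reported as non-significant. If the choice is instead left open until the data are in, two analysts could follow the same text and reach different conclusions at the 0.05 level.

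**Working it through.** **1. The stated sample size, as a check on the inputs.** Sample size calculation gives 32% against 68%, 80% power and "a one-sided significance level" of 0.025. In Statistical analyses, "A two-sided significance level will be set at" 0.05. Both imply the critical value 1.96. The unpooled normal formula gives

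n per arm = (1.96 + 0.8416)² × (0.32×0.68 + 0.68×0.32) / (0.68 − 0.32)² = 7.849 × 0.4352 / 0.1296 = 26.4, so 27 per arm or 54 in total. Then 54 / 0.9 = 60.

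Both stated figures reproduce. They concern the yes/no primary outcome; no power is stated for the grade.

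**2. Why the order is lost.** The Pearson statistic is Σ(O − E)²/E over the eight cells. Permuting the grade columns leaves it unchanged, and it has (2 − 1)(4 − 1) = 3 degrees of freedom. Mann–Whitney uses the ranks and tests for a shift in one direction or the other.

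**3. Assumptions for the grade.** The documents give the share with any sore throat but not its split by severity. The splits of the 68% of controls affected into mild/moderate/severe are therefore assumed: 60/30/10, 70/25/5, 50/35/15 and even. Example for 60/30/10:

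- Control: 0.32 none; 0.68×0.6 = 0.408 mild; 0.68×0.3 = 0.204 moderate; 0.68×0.1 = 0.068 severe.
- A proportional-odds shift to 32% affected needs OR = (0.68/0.32)/(0.32/0.68) = 4.52.
- CPMA: 0.68, 0.244, 0.061, 0.016.

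With 30 per arm, the expected number of severe grades is 30×0.068 + 30×0.016 = 2.5 in both arms together, so that column is sparse.

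**4. Simulated power.** There were 20,000 trials per scenario at two-sided 0.05, comparing Pearson χ² on the 2×4 table with tie-corrected Mann–Whitney. Fisher's test on the 2×4 table was not simulated. Power is in percent; differences are taken before rounding.

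| Assumed effect | Control split | n per arm | χ² | Mann–Whitney | Difference |
|---|---|---|---|---|---|
| Proportional odds, 68% to 32% | 60/30/10 | 27 | 64.4 | 81.1 | +16.6 |
| Same | 60/30/10 | 30 | 69.0 | 84.9 | +15.9 |
| Same | even | 30 | 71.6 | 86.0 | +14.3 |
| Proportional odds, OR 2 | 70/25/5 | 27 | 16.3 | 26.0 | +9.7 |
| Proportional odds, OR 3.5 | 60/30/10 | 30 | 51.9 | 71.0 | +19.1 |
| 68% to 32%, severity mix of those affected unchanged | 60/30/10 | 27 | 61.1 | 71.6 | +10.6 |
| Same | 60/30/10 | 30 | 66.0 | 76.2 | +10.2 |
| Any sore throat unchanged at 68%, milder among those affected | constructed | 30 | 49.8 | 24.0 | −25.8 |
| Fewer mild only, moderate and severe unchanged | constructed | 30 | 81.6 | 56.1 | −25.5 |

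Over all four splits and both sample sizes the gain from Mann–Whitney was:

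- 14 to 17 points for the proportional-odds shift at the protocol's rates;
- 10 to 19 points for odds ratios 2 to 3.5;
- 10 to 11 points when the severity mix is unchanged.

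In the two constructed non-uniform scenarios it was a loss of 23 to 26 points.

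**The case against.** A reader might infer that the article assigns the grade to χ²/Fisher. It does not. The variables named as categorical are four incidences, and the χ² sentence refers back to them. The list is only illustrative, so χ² is not excluded, but nothing puts the grade there. The 0–10 pain score is not strictly continuous either, and few would analyse it as a 2×11 table. The 0–3 grade is also coded numerically, so an analyst could reasonably take it to Mann–Whitney as a non-normal score. This objection stands: the χ² route is a literal reading, not a stated assignment.

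A reader might also infer a fixed loss of 15 to 19 points of power. The documents do not support that. They contain no grade distribution and no severity effect, and proportional odds is a model that favours Mann–Whitney. With an unchanged severity mix the gain is only 10 to 11 points, and it can change sign.

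Nor would a χ² result leave the reader without direction. Counts and percentages by arm would show it descriptively, although the test would not.

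Finally, an analysis plan not shown may name the test, and leaving a secondary outcome's test to that plan is normal. That would settle the point in practice. But the article is not silent on tests: it sets out a rule by variable type, and the rule does not fit one of its own listed outcomes.

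**Conclusion.** The point holds in a limited form. The test rules contain no ordinal route, Mann–Whitney is tied to continuous variables, and the literal reading leaves the 0–3 grade to an unordered test. The cost is roughly 10 to 19 points of power at 27 to 30 per arm. That range rests on assumed control grades and on an effect that shifts patients toward milder grades or lowers incidence with the severity mix unchanged. It is not a property of the documents, and it reverses for some non-uniform effects. Severity is minor: one secondary outcome is affected. The primary outcome is yes/no and is properly tested by χ²/Fisher, and the 54 and 60 patients are unaffected.

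**What to change.** Add one sentence to Statistical analyses, for example: *The 0–3 sore-throat intensity grade will be compared between groups with the tie-corrected Mann–Whitney U test; χ² or Fisher's exact test is used for the yes/no outcomes only.* A proportional-odds model reporting a common odds ratio with its 95% CI is a sound alternative; whichever is chosen should be named before the data are analysed. Because an effect might not be a uniform shift, show the full grade distribution by arm beside the test.

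The change costs nothing beyond the sentence. Mann–Whitney is already in the plan, and no further patients or data are needed. If the full analysis plan already names an ordinal method for the grade, the article need only be brought into line with it.
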